## Abstract

**Introduction:**

Over 50% of patients participating in cardiac rehabilitation (CR) experience poor sleep and/or, closely related, psychological stress. Although stress management interventions are generally available, they are typically underutilised in CR, and sleep remains an underaddressed component within CR. This is concerning, as poor sleep and stress not only reinforce each other but are also associated with poorer cardiovascular health and lower quality of life. Therefore, the primary aim of the OPtimising CArdiac REhabilitation by REfining Sleep and STress (RESST) study is to investigate the (cost-)effectiveness of adding a behavioural intervention targeted at improving sleep and managing stress during CR (RESST intervention) on sleep and psychological stress. Furthermore, the study aims to explore the (bidirectional) associations between sleep, stress and lifestyle behaviours.

**Methods and analysis:**

This parallel-arm multicentre randomised controlled trial will include 200 CR patients across 3 major CR centres in the Netherlands who experience poor sleep and/or stress. Patients will be randomised in a 1:1 ratio to standard CR or standard CR with the RESST intervention. Standard CR is a structured programme combining exercise, lifestyle guidance and risk management. On top of standard CR, the RESST intervention consists of 5 in-person group sessions targeting sleep and stress and is based on Acceptance and Commitment Therapy and Cognitive Behavioural Therapy. Primary outcomes are accelerometer-assessed and self-reported sleep and perceived stress. Secondary outcomes include quality of life, psychosocial well-being, chronic stress biomarkers (hair cortisol and cortisone), momentary fatigue, momentary stress and physical activity. Linear mixed models will be used to assess changes in outcomes at 3-month (after intervention and/or CR completed) and 6-month follow-up. The momentary data collected with ecological momentary assessment and accelerometry will be analysed using multilevel linear mixed models to explore the (bidirectional) relationship between sleep, stress and other lifestyle components such as physical activity.

**Ethics and dissemination:**

This study was approved by the ethics committee of Erasmus MC, Erasmus University Medical Centre, Rotterdam, the Netherlands (MEC-2024-0238). The findings will be disseminated through publications in peer-reviewed journals, presentations at academic conferences and professional and patient publications.

**Trial registration number:**

NCT06505109.

Strengths and limitations of this studyCombination of objective and self-reported assessment of the primary outcomes, sleep and stress, to minimise bias and provide multifaceted insight into these factors.Use of ecological momentary assessment to determine associations in a daily life context between sleep, stress and lifestyle behaviours such as physical activity and diet.The REfining Sleep and STress intervention is aligned with existing cardiac rehabilitation practices, enhancing the potential for future implementation in standard care.Study participants cannot be blinded due to the behavioural nature of the intervention.Follow-up time is 6 months, limiting the possibility to assess long-term cardiovascular health outcomes.

## Introduction

 Cardiac rehabilitation (CR) focuses on the secondary prevention of cardiovascular disease through a multidisciplinary approach that includes exercise training, psychosocial counselling and lifestyle education and modification.^1^ CR was shown to reduce mortality and hospital (re)admissions, and to improve quality of life (QoL) in a cost-effective manner for cardiac patients.^1^,^5^ However, despite these benefits, 10%–30% of patients experience recurrent cardiovascular events or require cardiac surgery after completing CR, indicating the need for further optimisation.^5 6^

One area with clear potential for further improvement is sleep, as this is generally unaddressed in current CR programmes. Yet, more than half of cardiac patients experience poor sleep,^7 8^ with one study reporting numbers as high as 87%.^9^ In comparison, it is estimated that around one-third of the general population experiences poor sleep.^10^,^12^ Poor sleep has been associated with lower cardiovascular health and a 50% increased risk of a recurrent cardiac event,^13 14^ as well as lower QoL, lower treatment adherence and lower self-efficacy, which may impede the effectiveness of CR.^7 15^

Similar to sleep, and highly interconnected,^16^ psychological stress is also widely present in patients with cardiovascular disease. A large meta-analysis estimated that psychological stress affects 58% of all cardiac patients.^17^ Moreover, long-term stress has been shown to predict future cardiovascular disease.^18^ Stress management programmes are often available during CR^1^ and have been shown to improve perceived stress, anxiety and depression and reduce cardiovascular event rates by 50%.^19 20^ However, stress management training during CR is often underused,^21 22^ leaving patients without the support they may need.

Despite the strong interconnection between sleep and stress, interventions that target only sleep or only stress are often insufficient to optimally improve either. A study has shown that 85% of CR participants following stress management training experienced poor sleep, and that the training was less effective in improving stress in those patients with insomnia.^23^ Similarly, long-term improvements in insomnia severity after cognitive behavioural therapy for insomnia (CBT-i) were less likely to be sustained among those who also experienced stress.^24^ These findings suggest that combined targeting of sleep and stress may be required to effectively address these often co-occurring complaints.

Beyond assessing the effectiveness of interventions addressing both sleep and stress, it is important to explore the underlying mechanisms by examining how these factors interact. Accumulating evidence indicates a bidirectional relationship between sleep and stress.^25^ Day-to-day studies in healthy adults, for example, showed that higher evening stress predicts shorter subsequent sleep, while poor sleep increases next-day stress.^26^ Sleep and stress may also interact with other lifestyle behaviours central to CR. For example, it has been suggested that daytime physical activity can influence sleep quality, potentially moderated by perceived stress,^27 28^ whereas sleep during the night can influence physical activity levels the following day.^29^ Last, parameters of diversity, such as sex, age, ethnicity and socioeconomic status, may also influence the effectiveness of interventions.^16 30^ A better understanding of how lifestyle factors and diversity parameters are intertwined with sleep and stress can be used to optimise and tailor behavioural interventions for sleep and stress, as well as CR programmes.

The primary aim of the OPtimising CArdiac REhabilitation by REfining Sleep and STress (OPTICARE-RESST) trial is to determine the effectiveness of integrating a behavioural programme targeting sleep and stress simultaneously (RESST-intervention) into CR. We hypothesise that the intervention will not only improve sleep and stress, but also improve cardiometabolic health, lifestyle behaviours and psychosocial well-being. Moreover, we expect this intervention to be cost-effective as it may reduce (mental) healthcare uptake, hospital admissions and mortality, while improving QoL. Secondary aims are to examine the bidirectional relationships between sleep, stress and lifestyle factors to get more insight into the working mechanisms; determine whether aspects of diversity are associated with intervention effectiveness; and identify barriers and enablers of the intervention relevant to implementation in practice.

## Methods and analysis

### Design

OPTICARE-RESST is a multicentre randomised controlled trial (RCT). Patients will be recruited from three large CR centres across the Netherlands: Capri Cardiac Rehabilitation in Rotterdam and in The Hague, and Máxima Medical Centre in Veldhoven/Eindhoven. Participants are randomly allocated in a 1:1 ratio to a 6–12 week standard CR programme (control group), or a standard CR programme with an additional behavioural intervention to improve sleep and manage stress (intervention group). A total of 200 participants will be included (figure 1). All participants need to provide signed informed consent before study entry (online supplemental material). Data are collected at the start of CR (baseline), at 3 months (post-CR) and at 6 months.

**Figure 1 F1:**
[figure not shown]
Flow chart of the study inclusion process. CR, cardiac rehabilitation; PSQI, Pittsburgh Sleep Quality Index; PSS-10, 10 item Perceived Stress Scale; RESST, REfining Sleep and STress.

The study was registered at ClinicalTrials.gov (NCT06505109) prior to trial initiation. The protocol was written using Standard Protocol Items: Recommendations for Interventional Trials reporting guidelines (online supplemental material).^31^ Ethical approval was obtained from the ethics committee of Erasmus MC, Erasmus University Medical Centre, Rotterdam, the Netherlands (MEC-2024-0238).

### Patient population and randomisation

To be eligible for inclusion, participants need to (1) participate in CR at one of the study centres for any cardiac diagnosis or reason as stated in the Dutch guidelines,^1^ (2) be at least 18 years of age, (3) be proficient in the Dutch language, (4) experience poor sleep (Pittsburgh Sleep Quality Index (PSQI) >5^32^) or psychological stress (Perceived Stress Scale-10 (PSS-10) >13^33 34^) and (5) be willing to provide signed informed consent before study entry. Exclusion criteria are (1) having a severe psychiatric, cognitive or physical comorbidity that would impede CR participation and (2) active treatment for sleep disorders, stress or other forms of (behavioural) therapy at the start of the study or expected to start within 6 months that could interfere with the RESST intervention. Participants who have received prior treatment targeting sleep, stress or a related complaint (eg, continuous positive airway pressure users or sleep medication), that is still ongoing and has resulted in symptom stability in the past 3 months, are eligible.

Participants who fulfil inclusion and exclusion criteria are randomised (1:1) to the control or intervention group after baseline measurements are completed. Randomisation is performed using Castor software, which generates a random allocation sequence in variable blocks of 2, 4 and 6, stratified by participating centres. First patient inclusion took place on 28 August 2024 and is expected to last for a period of 2 years.

### Control group

The control group will receive standard CR. Participating centres adhere to the Dutch CR guidelines,^1^ which are largely in line with the guidelines of the European Society of Cardiology,^35^ as well as the guidelines of the American Heart Association.^36^ Standard CR programmes consist of 6–12 weeks of twice-weekly supervised, group-based exercise sessions and educational sessions on cardiovascular risk factors, living with cardiovascular disease and medication use, healthy lifestyle and coping. The duration of the CR programme is based on the needs and complexity of the patient. Group counselling is available when indicated e.g., on stress management or relaxation, and a healthy diet, as well as individual guidance from a social worker or occupational therapist, psychologist or dietitian. Referral for smoking cessation is possible if needed.

### Intervention group

The intervention group receives the RESST intervention in addition to standard CR (figure 2). The RESST intervention consists of five group sessions lasting 120 min each, under the guidance of a trained psychologist or social worker.

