### Sample size

The chosen sample size was based on expected differences in three somewhat related primary endpoints. We aim to detect an effect on at least one of these endpoints with a power of 80%. Therefore, for each comparison, a two-sided alpha of 0.017 was used.

Regarding sleep duration, the estimated mean±SD at 3-month measurement is 6.2±0.9 hours for the control group.^47^ We hypothesised that this value would be 10% higher for patients randomised to CR+RESST, equating to 6.8±0.9 hours at 3-month measurement. To detect this mean difference of 0.6 hours, 49 participants per group are needed. Regarding sleep quality, the expected mean PSQI score is 6.5±2.6 at 3-month follow-up for the control group, and 4.4±2.6 for the intervention group, based on research by Ghane *et al* and unpublished data from the OPTICARE-XL trial.^48^ To detect this mean difference in PSQI of 2.1 points between the control and intervention group, 68 participants are required. For the last primary outcome, perceived psychological stress, we expect a mean PSS-10 score of 15.4±8.2 is expected after CR alone, and a mean score of 11.1±8.2 for the intervention group.^19^ To detect this mean difference of 4.3 points, 156 participants are required. Thus, accounting for a minimum of 156 participants and a dropout of approximately 25%,^49 50^ we plan to include 200 participants in the study. This sample size will also allow us to take a number of covariates into account which may be associated with intervention effectiveness.

Drop-out and adherence will be continuously monitored throughout the study. If both remain lower than expected, participant inclusion may be stopped before reaching 200 participants to prevent unnecessary burdening.

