### Statistical analysis

Descriptive statistics will be used to summarise the outcomes of the primary and secondary study parameters, as well as baseline characteristics (table 2).

Primary analyses will be conducted according to the intention-to-treat principle, but per-protocol analysis will be conducted to provide further insight into the effectiveness in adherent participants, as we aim to continue collecting data from non-adherent participants.

Linear mixed effect (LME) models will be used to study between-group differences in changes in primary and secondary endpoints between T0-T3m (primary analysis) and T0-T6m (secondary, explorative analysis). LME models can handle missing data and do not require data imputation.

To investigate whether parameters of diversity (age, sex and socioeconomic status) predict differences in changes in sleep and stress parameters between the intervention and control groups, an interaction term between randomly allocated treatment and the determinant of interest will be added to the LME model. If a significant interaction emerges, exploratory subgroup analyses may be performed.

A cost-effectiveness analysis will be performed using a healthcare and societal perspective according to the latest Dutch guidelines.^51^ A short-term time horizon of 6 months (total follow-up) will be analysed, as well as a lifetime time horizon, by using mathematical modelling for extrapolation beyond the follow-up period.^52^ Costs will include healthcare utilisation, intervention costs and productivity losses, while effects will be expressed in quality-adjusted life-years.

LMEs will also be used to examine the (bi)directional relationships between sleep, stress and lifestyle/health components. Lifestyle and health components include physical behaviour, diet intake and momentary fatigue. First, cross-sectional and longitudinal associations will be assessed using weekly averages of sleep/stress parameters and other lifestyle/health components. Additionally, day-to-day temporal relationships will be studied, while measurements on a certain moment may serve as a predictor for outcomes on a later moment. In these analyses, an outcome on a certain moment (eg, physical activity) may serve as the predictor for sleep/stress at a later moment during the day or on the following night/day, or conversely, sleep/stress at a certain moment may serve as the predictor for an outcome (eg, fatigue) during a later moment.

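### RESST is delivered in facilitator-led groups in one arm only, but the sample size assumes independent patients and no course-group term is named for the primary model

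*Protocol article*

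**What the plan says.** **Delivery.** Under Intervention group: "The RESST intervention consists of five group sessions lasting 120 min each, under the guidance of a trained psychologist or social worker". Under Control group, the care that both arms receive is itself partly group-based: "Standard CR programmes consist of 6–12 weeks of twice-weekly supervised, group-based exercise sessions and educational sessions".

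**Allocation.** Under Patient population and randomisation, individual participants "are randomised (1:1) to the control or intervention group after baseline measurements are completed". The software "generates a random allocation sequence in variable blocks of 2, 4 and 6, stratified by participating centres". Patients are thus randomised one by one, and centre is the only stratification factor.

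**Sample size.** The goal is worded as "We aim to detect an effect on at least one of these endpoints with a power of 80" per cent. The error level follows: "Therefore, for each comparison, a two-sided alpha of 0.017 was used". Three comparisons of means are then given: sleep duration (difference 0.6 h, SD 0.9 h, 49 per group), PSQI (difference 2.1, SD 2.6, 68 in total) and PSS-10 (difference 4.3, SD 8.2). PSS-10 sets the trial size: "To detect this mean difference of 4.3 points, 156 participants are required". With about 25% dropout the plan is 200. No group size, number of courses, ICC or design effect appears.

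**Analysis.** Under Statistical analysis: "Linear mixed effect (LME) models will be used to study between-group differences in changes in primary and secondary endpoints between T0-T3m (primary analysis", with the 6-month comparison as secondary and exploratory. No random-effects structure is given. A term for course group, facilitator or centre is neither included nor excluded.

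**The concern.** Individual randomisation followed by group treatment in one arm gives a partially nested design. Patients in the same RESST course share a facilitator, peers and exercises, so part of the outcome variation may belong to the course rather than the patient. Stratifying by centre does not remove it. The group-based exercise of standard CR does not cancel it either, because both arms receive that and RESST adds a level in one arm only.

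Two things are at stake. First, a model with no course-group term would understate the variance of the intervention-arm mean. The 0.017 level is the trial's protection across three primary endpoints, so an inflated error on each test weakens that protection. Second, PSS-10, the endpoint that fixes the trial size, would have less power than its stated number implies. The Sample size section also allows recruitment to stop short of 200, and the 156 against which that would be judged has no clustering allowance.

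**Working it through.** **1. Reproduce the stated numbers.** Two-sample t-test, independent patients, two-sided alpha 0.017, power 80%; inputs from the Sample size section.

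| Endpoint | Difference / SD | d | n per group | Stated |
|---|---|---|---|---|
| Sleep duration | 0.6 / 0.9 | 0.667 | 48.3, so 49 | 49 per group |
| PSQI | 2.1 / 2.6 | 0.808 | 33.4, so 34 | 68 in total |
| PSS-10 | 4.3 / 8.2 | 0.524 | 77.2, so 78 | 156 in total |

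All three match, so the calculation contains no design effect.

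**2. Is there a reserve for PSS-10?** 156 / 0.75 = 208, and 200 × 0.75 = 150 evaluable. At 75 per arm, t-test power is 78.6% before any clustering, so there is none.

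**3. Add clustering in the intervention arm only.** Group size m and the ICC are my assumptions: m = 6 to 10, ICC = 0.01 to 0.10. With n = 78 per arm and z(0.9915) = 2.387, in SD units:

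- DE = 1 + (m − 1) × ICC
- true SE = √[(DE + 1) / 78]; SE ignoring groups = √(2 / 78) = 0.1601
- ratio R = √[(1 + DE) / 2]
- true error of the nominal 0.017 test, if groups are ignored = 2 × [1 − Φ(2.387 / R)]
- power, if groups are modelled = Φ(d / true SE − 2.387)

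Example, m = 8 and ICC = 0.05: DE = 1 + 7 × 0.05 = 1.35. True SE = √(2.35 / 78) = 0.1736. R = 1.084, so the SE that ignores groups is about 8% too small. True error = 2 × [1 − Φ(2.202)] = 0.028. PSS-10 power = Φ(0.524 / 0.1736 − 2.387) = Φ(0.634) = 73.7%.

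The last column below uses Satterthwaite degrees of freedom, with 78 / m courses in the intervention arm and 78 patients in the control arm, and the noncentral t distribution. In the example this is 25.0 degrees of freedom.

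| m | ICC | DE | R | True error if groups ignored | PSS-10 power, normal | PSS-10 power, few-group df |
|---|---|---|---|---|---|---|
| any | 0 | 1.00 | 1.00 | 0.017 | 81.3% | – |
| 6 | 0.01 | 1.05 | 1.01 | 0.018 | 80.2% | 76.8% |
| 8 | 0.02 | 1.14 | 1.03 | 0.021 | 78.2% | 73.2% |
| 8 | 0.05 | 1.35 | 1.08 | 0.028 | 73.7% | 67.8% |
| 8 | 0.10 | 1.70 | 1.16 | 0.040 | 66.7% | 59.6% |
| 10 | 0.05 | 1.45 | 1.11 | 0.031 | 71.6% | 63.5% |
| 10 | 0.10 | 1.90 | 1.20 | 0.048 | 63.0% | 53.3% |

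**4. Check against the declared goal.** At 75 evaluable per arm, PSQI power is 98.5% at m = 8, ICC 0.05, and 95.7% at m = 10, ICC 0.10 (normal approximation; 97.1% and 90.5% with few-group degrees of freedom). PSQI alone therefore secures 80% power for at least one endpoint over the whole assumed range.

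**The case against.** The strongest objection concerns the model. A reader might infer that the mixed models treat intervention patients as independent and that the standard errors are therefore wrong. The article does not say so. It gives no random effects at all, it is a condensed text, and it refers to a data analysis plan to be discussed with a biostatistician. This objection stands: the error inflation is conditional on the model omitting the term. It does not reach the sample size, which is a published calculation and demonstrably assumes independence.

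A reader might also infer that the stated 80% power cannot be reached. That is not supported, because the declared goal is an effect on at least one endpoint and step 4 shows that it holds. Only the PSS-10 figure suffers.

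Third, the PSS-10 calculation uses the raw 3-month SD, while the planned model also uses baseline. Assuming a baseline correlation of 0.5 (not in the document; variance × 0.75), power at 78 per arm would be about 86% at m = 8, ICC 0.05, and about 77% at m = 10, ICC 0.10. So some or all of the loss may be recovered. Baseline adjustment does not, however, correct the type I error of a model that ignores groups.

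Fourth, the size is uncertain. At ICC 0.01 to 0.02 with 8 per group, PSS-10 loses only about 2 to 3 points by normal approximation and the error is 0.019 to 0.021. Nor does the article say that courses have fixed membership or one facilitator throughout, so a RESST-only random effect is a reasonable model rather than the only one.

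**Conclusion.** The point holds in conditional form. What the document shows outright is that one arm is treated in facilitator-led groups and that the sample sizes make no allowance for this. What depends on the final model is the error rate. With no course-group term and an ICC above zero, standard errors are too small, and the nominal 0.017 becomes about 0.018 to 0.048 for an assumed 6 to 10 per group and ICC 0.01 to 0.10. Over the same range, PSS-10 power at 156 evaluable is about 80% down to 63% by normal approximation, and about 77% down to 53% with few-group degrees of freedom, before any gain from baseline adjustment.

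The trial's declared power goal survives through PSQI, and nothing here invalidates the design or calls for more patients. This is a worthwhile and inexpensive improvement to settle before analysis, not a critical defect.

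**What to change.** - Record the RESST course-group identifier, and the facilitator, for each intervention patient. Session attendance is already taken from health records, so this should be recoverable for patients already enrolled.
- Prespecify, before the analysis (which will not be blinded), a partially nested primary mixed model: a random course-group effect in the RESST arm, with Satterthwaite or Kenward-Roger degrees of freedom. If membership or facilitators change within a course, state how the patient is assigned.
- Restate PSS-10 power over an ICC range of 0.01 to 0.10 with the expected group size, and say what baseline correlation is credited, if any.
- Keep the planned 200 patients.

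The cost is one data field and a few lines in the analysis plan. The downside is slightly wider confidence intervals and a less favourable stated power for PSS-10.
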